##### Hand Grip Strength (HGS)

At T0, T2, and T4, participants will complete an assessment of their HGS as measured by the amount of static force individuals can generate with one hand via a Jamar digital dynamometer (Patterson Medical, Kenora, ON, Canada) with a standardized protocol [96]. HGS measurements are reliable when standardized methodology and calibrated equipment are utilized. The participants will be instructed to sit in a chair holding the dynamometer with a 90-degree angle at the elbow. The dynamometer’s position two (counted from the display) of five possible settings will be used. Three measurements will be collected for each hand, resulting in a total of six measurements alternating between the right and left hands. A trained researcher will conduct the assessment.

##### Stool Sample Collection, Storage and Analysis

Stool sample kits, a Bristol Stool Form Scale (BSFS), and instructions will be provided to the participants at the screen visit. BSFS, with its accompanying illustrations, was developed in 1997 and has become a widely used practical guide to classify stools into seven groups on the basis of the evidence that the appearance of stools is dependent on the length of time that it spends in the colon, as reported previously [97]. The participants will collect the samples at home within the preceding 24–72 h of their T0, T2, T4, and T5 visits and indicate their stool type on collection containers as per BSFS, the date, and the time of stool passage. The samples will be stored at −20 °C until they are ready to be brought back. Stool samples will be shipped to an external laboratory for processing and analyses of SCFAs, probiotic strain deoxyribonucleic acid (DNA), and the gut microbiome using 16s and metagenome sequencing to verify intake of the IP by the intervention group. The samples will be run in triplicate.

##### Oral Glucose Tolerance Test (OGTT)

A further subset of participants (15 per arm, 30 in total) will be invited to participate in a musculoskeletal subgroup, involving an additional assessment of a 2-h OGTT at T0, T2, and T4 [98,99]. Blood samples will be collected into tubes containing ethylenediaminetetraacetic acid for the analysis of glucose, glucagon-like peptide-1 receptor agonist, peptide YY, and adiponectin (Figure S6) at the completion of the trial. The samples are shipped to an external facility for analysis.

### 2.8. Sample Size

The sample size calculation was based on data from a previous probiotic intervention study in older women, which demonstrated a significant effect on bone health outcomes. For this study, additional metabolic outcomes are included, and effect sizes for these outcomes were estimated based on prior research using similar synbiotic interventions in comparable populations.

Permitting for possible participant attrition, the total sample size for the trial will be 160 (80 per arm), taking a 20–30% drop-out rate into account. Statistical power analysis will be performed in relation to the primary outcome of the relative twelve-month change (%) in total BMD using HR-pQCT at the distal tibia. On the basis of a similar probiotic intervention in older women [100], the expected decrease in tibia BMD is 1.85% in the placebo arm and 0.9% decline at most in the treatment arm, with a standard deviation (SD) of 1.6% and an alpha of 0.05; 46 participants are needed in each arm to achieve >80% power. To be able to detect smaller groups to group differences and to account for an attrition rate of 20–30% and due to many secondary outcomes, we will recruit a minimum of 80 participants into each arm.

### 2.9. Statistical Analysis

All outcomes and analyses will be prospectively categorized as primary, secondary, or exploratory. Categorical variables will be described by numbers and percentages and 95% confidence intervals (CIs) for percentages based on a binomial distribution. Continuous variables will be described by means, SDs, medians, minima, and maximums, and 95% CIs for the means. The main comparisons will be of the intervention vs. placebo. With respect to dichotomous variables, Fisher’s exact test will be used to compare between the two groups. For continuous variables, Fisher’s nonparametric permutation test will be used.

To address the concern regarding multiple comparisons, the statistical analysis plan will include methods to control for Type I error across the primary and secondary outcomes. The primary variables will be investigated as the percentage difference from T0 to T4 visit between the two study groups. The trial will be deemed positive if the intervention vs. placebo is significant at the 0.05 significance level. The primary variable is anticipated to be normally distributed and analyzed by applying analysis of covariance (ANCOVA) with the relative change from T0 to T4 as the dependent variable, the treatment group as the fixed effect, and the T0 value as the covariate. The least square means with 95% CIs for the active treatment group vs. the placebo group will be presented together with the associated *p*-value.

The secondary variables are continuous and possibly will not be normally distributed. For secondary outcomes, adjustments will be made using appropriate correction methods, such as the Bonferroni adjustment for family-wise error control or the Benjamini–Hochberg procedure for controlling the false discovery rate, depending on the degree of correlation between outcomes. This approach ensures the integrity of the analyses while accounting for the diversity of outcomes assessed in the study.

Primary and secondary analyses will be conducted for the intention-to-treat as well as the per-protocol population. The difference in parameter estimates between the intervention and the placebo will be assessed for its clinical relevance. The secondary analyses will be considered exploratory, and an alpha of 0.05 will be applied with no further adjustments.

Participants who supply both T0 and end-of-treatment samples will be included in a secondary dose–response analysis to account for early trial withdrawals or inadequate compliance.

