## 2. Materials and Methods

### 2.1. Trail Design

The trial is a randomized, double-blinded, placebo-controlled trial. Participants will be assessed at baseline (T0) upon recruitment and subsequently at five follow-up visits. The trial will be conducted in three, phases as summarized in Figure 2 and described in detail in Supplementary File S1.

Dual-energy X-ray absorptiometry (DXA) scans will be conducted on participants at screening. Following this, participants will be assigned randomly to either a synbiotic supplement or a matching oral placebo arm. The efficacy of the supplement will be established by comparing data collected after 12 months of treatment with those collected at T0. The study outcomes are illustrated in Figure 3. Only Caucasian women will be recruited in this trial owing to significant differences in BMD and bone remodeling between ethnicities and races.

The trial will be advertised on social media platforms, relevant public locations, and newspapers, and through assisted mail out of trial information conducted by a government agency to community-dwelling women aged 40–65 years residing in the inner suburbs of Melbourne, Victoria, Australia.

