##### Blood Biomarker Measurements

There will be three venous fasting blood collection timepoints (T0, T2, and T4) and three finger prick blood draws (screening, T2, and T4). Blood samples will be collected from the cubital vein by a qualified venipuncturist at a hospital pathology contracted by the researchers.

At T0, T2, and T4, blood samples will be tested for fasting blood glucose and insulin by the hospital’s pathology laboratory staff via a commercial enzymatic kit (Beckman Coulter Inc., Brea, CA, USA) with a CV of 1.6–2.6% and a chemiluminescent microparticle immunoassay Architect Insulin 8K41 kit (Abbott GmbH & Co., Wiesbaden, Germany) with a precision of ≤7% total CV. The remaining serum and plasma will be aliquoted and stored in a −80 °C freezer for further analysis. At the completion of the trial, these samples will be analyzed via commercially available immunosorbent assays for the following bone turnover markers: C-terminal cross-linking telopeptide of type I collagen, procollagen type 1 N-terminal propeptide, high-sensitivity C-reactive protein and osteocalcin at T0, T2, and T4. A flowchart of the blood collection and processing procedure is illustrated in Figure S5.

Furthermore, the first 80 randomized participants will undergo an additional blood analysis of the number of circulating regulatory T cells (Tregs) (n = 40 per arm). Blood for this analysis will be collected at T0 and T4, and this collection will not require an additional blood draw. Tubes will be spun by pathology staff before being sent by a courier to a collaborator for peripheral blood mononuclear cell isolation and storage in liquid nitrogen until completion of the trial [91]. Treg analysis will be subcontracted to an external facility at the completion of the trial.

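### The permutation test named for continuous secondary outcomes carries no baseline covariate, which gives up some precision that the data already collected could supply

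*Protocol article*

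**What the plan says.** Section 2.9 gives one method for comparing continuous variables between arms: Fisher's "nonparametric permutation test will be used". No covariate is attached to it. The section does not say whether the tested quantity is the T4 value or the change from T0.

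For the primary variable alone, the same section specifies ANCOVA with "the treatment group as the fixed effect, and the T0 value as the covariate". Of the rest it says: "The secondary variables are continuous and possibly will not be normally distributed". That is the only apparent reason for treating them differently.

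On the comparison intended, Section 2.1 speaks of "comparing data collected after 12 months of treatment with those collected at T0", which points to change from T0. On reporting, Section 2.9 adds: "The difference in parameter estimates between the intervention and the placebo will be assessed for its clinical relevance".

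Section 2.7.2 shows that baselines exist. For glucose and insulin, "At T0, T2, and T4, blood samples will be tested for fasting blood glucose and insulin". For grip strength, "At T0, T2, and T4, participants will complete an assessment of their HGS". Bone markers, cognition and the OGTT follow the same three visits. Continuous glucose monitoring has screening, T2 and T4. DXA (screening and T4) and regulatory T cells (T0 and T4) have a baseline but no T2 value.

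**The concern.** A pre-treatment measurement of the outcome is usually the strongest predictor of its later value. Using it as a covariate removes variation unrelated to treatment. The plan does this for tibial BMD but not for the other continuous outcomes, although the values are collected.

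The secondary outcomes carry weight in this trial. The abstract puts particular emphasis on blood glucose regulation, and Section 2.8 justifies 80 women per arm partly by the number of secondary outcomes. An avoidable loss of precision works against that rationale.

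There is also a reporting gap. Clinical relevance is to be judged from parameter estimates, but a bare permutation test returns a p-value. It does not by itself give a baseline-adjusted difference with a confidence interval.

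**Working it through.** **The plan's own figure.** Section 2.8 gives no sample size for any secondary outcome. Its primary figure reproduces: difference 1.85 − 0.9 = 0.95 percentage points, SD 1.6, two-sided alpha 0.05 and 80% power give 45.5 by the two-sample t-test, so 46 per arm (power 0.804). The primary calculation is not in question. With 20–30% attrition, 80 per arm leaves 64 to 56.

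**Inputs for the secondary outcomes.** The baseline-to-T4 correlation r is not given in the article, so r is an assumption, shown here from 0.3 to 0.9. The formulas take equal SDs at baseline and T4, and absolute change.

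**Variance of the treatment difference**, relative to comparing T4 values alone:

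- T4 value alone: 1
- change from T0: 2(1 − r)
- ANCOVA with the T0 value: 1 − r²

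Hence ANCOVA relative to change is (1 − r²) / [2(1 − r)] = (1 + r)/2, and ANCOVA relative to T4 alone is 1 − r². The extra women needed without adjustment is the reciprocal minus 1. For example, at r = 0.5 on the change reading, 1/0.75 − 1 = 33%; at r = 0.8, 1/0.90 − 1 = 11%.

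The power columns use 56 per arm and, at each r, the effect that ANCOVA detects with 80% power: 2.8016 × √(2/56) × √(1 − r²) SD units.

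| Assumed r | Extra women, change tested | Extra women, T4 alone tested | Power, change | Power, T4 alone |
|---|---|---|---|---|
| 0.3 | 54% | 10% | 62% | 76% |
| 0.5 | 33% | 33% | 68% | 68% |
| 0.7 | 18% | 96% | 73% | 52% |
| 0.8 | 11% | 178% | 76% | 39% |
| 0.9 | 5% | 426% | 78% | 23% |

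Baseline adjustment is more precise in every row. The two readings cost the same at r = 0.5; above that, the T4-only reading costs more.

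**Simulation check** (2,000 trials, 499 permutations each; normal data, 56 per arm, r = 0.7, effect 0.378 SD). Power was 51% permuting T4 values, 74% permuting change, 79% permuting baseline-adjusted residuals and 80% for ordinary ANCOVA. Adjustment and permutation can therefore be combined with almost no loss.

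**Does non-normality require the simpler test?** With log-normal data, r = 0.7 and no treatment effect, the type I error of the four methods ranged from 4.5% to 5.3% at 56 per arm and from 4.4% to 5.7% at 15 per arm. The simulation error at a true 5% is √(0.05 × 0.95/2000), about 0.5 percentage points, so none departs clearly from 5%. This covers one skewed distribution only; power under skewness was not simulated.

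**The case against.** The planned test is valid. It protects the type I error under the non-normality that the authors expect, which matters most for the OGTT subgroup of 15 per arm, where large-sample robustness cannot be taken for granted. A reader might infer that the permutation test brings no benefit; that goes too far. What stands against the plan is only that the same protection is available with the baseline covariate included.

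A reader might also take the T4-only column as the size of the problem, with 33–178% more women needed at r of 0.5 to 0.8. The article does not support that. It never says that T4 values alone are compared, and Section 2.1 and the primary endpoint both point to change. A change score already uses the baseline, so it would also be wrong to say that the plan ignores it altogether.

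Nor does the article say that T2 data are discarded. T2 is measured after randomization and cannot serve as a baseline covariate; for a 12-month contrast it helps mainly when T4 is missing. Repeated-measures modelling and missing-data handling are commonly left to an analysis plan, which is not shown here.

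Finally, Section 2.9 calls the secondary analyses exploratory, and the figure listing all outcomes is not available. The statement about baselines is therefore limited to outcomes whose schedule the text describes. These points lower the severity. They do not remove the finding, because the article names a method, and a more precise one is open to it with the same data.

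**Conclusion.** The concern holds in a limited form. For continuous secondary outcomes the article specifies a valid two-group permutation test without a baseline covariate, although a baseline is available. On the better-supported reading, change from T0, the cost is about 11–33% more women for equal precision at r of 0.8 down to 0.5, and about 5% at 0.9. It would be higher for measures with r below 0.5. If T4 values alone were compared, the cost would exceed this at any r above 0.5.

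The size rests on an assumed correlation, which will differ between outcomes, and on a tested quantity that the article leaves unstated. The direction does not depend on either. The primary analysis already adjusts for T0, so the primary conclusion is unaffected. This is a minor-to-moderate free improvement.

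**What to change.** State in the analysis plan that continuous secondary outcomes at T4 are compared by ANCOVA with the T0 value as covariate (the screening value for DXA and continuous glucose monitoring), on the log scale where the measure is skewed, and that the adjusted difference is reported with its 95% CI. That also supplies the estimate needed to judge clinical relevance.

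Where distribution-free inference is wanted, notably in the OGTT subgroup, obtain the p-value by permuting treatment labels for the adjusted coefficient. If the simple permutation test is kept, say whether change or the T4 value is tested.

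A repeated-measures model that includes T2 is optional. It is useful mainly where T4 is missing, and it need not extend to the microbiome sequencing data, for which a Gaussian model is not an obvious choice.

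The cost is wording and programming. The baseline values are already in the visit schedule, and the article reports the trial as still under way, so the change can be fixed before unblinding.

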## 3. Results

The trial is currently underway, and as such, results are not yet available.

## 4. Discussion

The development of evidence-based, safe, and acceptable prevention strategies at the population level to target multiple risk factors for osteoporosis, T2DM, and metabolic syndrome in women and the population in general, and to reduce the health and economic burden of the condition, is warranted. Osteoporosis and associated fractures are an increasing global public health concern, with the current practice being predominantly aimed at secondary prevention following fractures, rather than primary prevention at the community level [101]. Similarly, the burden of metabolic diseases such as T2DM is increasing globally, and a rate higher in developed regions, including Western Europe, warranting urgent public health and clinical preventive measures [40].

Recent trials focusing on supplementation of postmenopausal women with probiotics have reported that it may increase BMD, with the evidence for it being stronger in women with osteopenia than osteoporosis. A randomized trial of three months of supplementation with *Bifidobacterium animalis* subsp. *lactis* amongst 40 postmenopausal women reported no significant change in BMD, but co-administering the probiotic with conventional drugs was found to be beneficial in managing postmenopausal osteoporosis, suggesting a beneficial mechanism of probiotic adjunctive treatment [102]. Moreover, a significant decrease in bone turnover markers following daily consumption of *Lactobacillus acidophilus* for three months in a randomized trial of 55 postmenopausal women has been reported [103]. Similarly, Vanitchanont et al. examined a three-month supplementation of 40 osteopenic postmenopausal women with a multispecies probiotic [104]. reported a significant decrease in the serum bone resorption marker (C-terminal telopeptide of type I collagen) compared to baseline and suggested that supplementation with multispecies probiotics may have a preventive effect on bone through their antiresorptive effects. Though these studies are limited by a small number of participants and short intervention periods, we note a study conducted by Glogowska-Szelag et al. amongst 172 postmenopausal women [105]. They described a decrease in T-score of the lumbar spine measured by DXA following 12 months in the placebo but not the probiotic group, suggesting that the oral administration of a mix of two species of *Lactiplantibacillus* may be a viable strategy for prevention of BMD loss.

This trial is the first RCT to investigate the effects of Pendulum WBF-038 for the prevention of osteoporosis and improvement of metabolic health following a 12-month treatment period. This trial is designed to: (i) provide greater insight of the link between the GM and bone health; (ii) evaluate the effectiveness of the effects of a dietary supplement in altering the gut microbiome to improve bone and metabolic health in postmenopausal women and consequently reduce or eliminate the risk factors for metabolic syndrome, including high blood pressure, high blood glucose, and a large waistline; (iii) investigate the potential effect of the trial intervention on immune system modulation as a potential mediator; and (iv) increase the capability for community-based health care professionals to implement evidence-based and probiotic-based therapies for the prevention and management of osteoporosis and T2DM management. It is expected that the findings of this trial will provide scientific evidence for the use of synbiotic supplements in the primary care of postmenopausal women at risk of developing osteoporosis as well as in the management of T2DM patients.

## Figures and Tables

**Figure 1 nutrients-16-04219-f001:**
[figure not shown]
Complications of gut microbiota dysbiosis. CKD = chronic kidney disease; IBD = inflammatory bowel disease.

**Figure 2 nutrients-16-04219-f002:**
[figure not shown]
Summary of OsteoPreP trial visits and activities. AE = adverse event; Ax = assessment; Hx = history; IP = investigational product; HbA1c = glycated hemoglobin; BP = blood pressure; BMI = body mass index; HWR = height-to-weight ratio; DXA = dual-energy X-ray absorptiometry; HR-pQCT = high-resolution peripheral quantitative computed tomography; CGM = continuous glucose monitor; Glu = glucose; vit B12 = vitamin B12; Treg = T regulatory cell; OGTT = oral glucose tolerance test; ^ = musculoskeletal subgroup.

**Figure 3 nutrients-16-04219-f003:**
[figure not shown]
Summary of OsteoPreP trial primary and secondary outcomes. BP = Blood pressure; DASS-21 = Depression Anxiety Stress Scale-21; EQ-5D = EuroQOL Five Dimensions quality of life scale; SIAS = Social Interaction Anxiety Scale; WEMWBS = Warwick-Edinburgh Mental Wellbeing Scale; Pain VAS = Visual Analogue Scale for pain; BMD = Bone Mineral Density; DXA = Dual-energy X-ray Absorptiometry; HR-pQCT = High-Resolution Peripheral Quantitative Computed Tomography; CGM = Continuous Glucose Monitor; OGTT = Oral Glucose Tolerance Test; HbA1c = Hemoglobin A1C blood sugar (glucose) level test; ^ = musculoskeletal subgroup at twelve months only; SCFA = Short Chain Fatty Acids; GLP-1 = Glucagon-Like Peptide-1 receptor agonist; GSRS = Gastrointestinal Symptom Rating Scale; * = musculoskeletal subgroup will undergo OGTT.

**Figure 4 nutrients-16-04219-f004:**
[figure not shown]
OsteoPreP trial inclusion and exclusion criteria and screening process. * Do not meet the inclusion criteria; ^ = DXA, BP, or HbA1c ineligible participant; Dx = diagnosis; DXA = dual-energy X-ray absorptiometry; COPD = chronic obstructive pulmonary disease; IBD = inflammatory bowel disease; CD = celiac disease; T1DM = type 1 diabetes mellitus; T2DM = type 2 diabetes mellitus; CLD = chronic liver disease; HbA1c = hemoglobin A1C blood sugar (glucose) level test; BP = blood pressure; HRT = hormone replacement therapy; RANK = receptor activator of NF-κB ligand; SERMs = selective estrogen receptor modulators.

**Table 1 nutrients-16-04219-t001:** Summary of the OsteoPreP trial questionnaires.

Questionnaire	Collection Method	Data Collection Timepoint						
		Screen	Baseline T0	3 Months T1	6 Months T2	9 Months T3	12 Months T4	Final * T5
Demographic data	SSI	X						
Medical History	SSI	X					X	
Current Medications	SR and SSI	X	X	X	X	X	X	X
Risk of future fracture	In person via FRAX^®^	X					X	
IPAQ-SF	SR		X		X		X	
Dietary surveys (DQES v3.2, FFFQ, GSRS)	SR		X	^a^ X	X	^a^ X	X	
Mental health and wellbeing surveys (SIAS, WEMWS, EQ-5D-5L, Pain VAS, DASS-21)	SR		X		X		X	

FRAX^®^ = The Fracture Risk Assessment Tool adopted for the Australian population [75]. IPAQ-SF = International Physical Activity Questionnaire-Short Form [76]. DQES v3.2 = Dietary Questionnaire for Epidemiological Studies [77,78,79]. FFFQ = Fermented Food Frequency Questionnaire. GSRS = Gastrointestinal Symptom Rating Scale [80,81]. DASS-21 = Depression, Anxiety, and Stress Scale-21 [82,83,84]. SIAS = Social Interaction Anxiety Scale [85,86]. WEMWS = Warwick-Edinburgh Mental Wellbeing Scale [87,88]. EQ-5D-5L = EuroQol Five Dimensions quality of life scale [89,90]. Pain VAS = Pain Visual Analogue Scale [90]. X = Signifies a timepoint at which questionnaire is administered. * T5 visits occur 24 days post 12 months (T4) visit. ^a^ Only GSRS surveys will be administered at T1 and T3. SSI = Semi-structured Interview. SR = Self-reported.

